### Statistical analyses and sample size considerations

The primary outcome comparisons of interest are between the in-person WWCM intervention and controls and the online WWCM intervention and controls. Subsequent analyses will compare outcomes between the in-person and online interventions. No adjustment for multiple testing will be performed [36].

### Clinical endpoints

#### Outcomes

Assessment of clinical effectiveness will include examination of changes in dichotomous outcomes (proportion of patients achieving 5% and 10% weight loss, prevalence of diabetes, hypertension, dyslipidemia, and sleep apnea as defined by lab parameters, patient report and/or use of active treatment) and continuous outcomes (anthropometric indices, blood pressure, lipid profile, glycemic control).

#### Data analysis

First, variables will be examined descriptively and graphically, including assessments of temporal trends and tests of normality. Second, the 3-month and 9-month mean change from baseline measures in each outcome will be calculated and compared between cases and controls using unpaired t-tests for continuous outcomes and chi-squared tests for dichotomous ones. Third, multivariable predictors of the 9-month change in a given outcome will be identified using appropriately constructed and calibrated linear regression models for continuous outcomes or logistic regression models for dichotomous ones. Herein, we present a detailed example of our modelling strategies for body weight. First, the proportion of patients achieving 5% weight loss (5% responders, a value widely considered as a clinically worthwhile weight change) [10] and the mean 9-month change in weight will be calculated in each study arm. Second, chi-square tests will examine for significant differences between cases and controls in 5% response rates and unpaired t-tests will examine for significant differences in mean body weight change scores. Third, a multivariable logistic regression model for 5% responders and a linear regression model for mean body weight will be constructed to examine the independent effect of the WWCM program on the 9-month change in 5% response rate or mean body weight, adjusting for any statistically significant (P<0.1) or clinically important between group differences. Missing data for weight change will be addressed using a conservative ‘baseline-value carried forward’ approach and examined in a sensitivity analysis using group mean-imputation methods to confirm the robustness of results [37]. All analyses will be conducted according to the “intention to treat principle”. No interim analyses, for either efficacy or futility purposes, have been planned.

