**Methods/Design:**

This pragmatic, prospective controlled trial will enrol 660 wait-listed subjects (220 per study arm) from regional bariatric programs in Alberta and randomly assign them to: 1. an in-person, group-based intervention (9 modules delivered over 10 sessions); 2. a web-based intervention (13 modules); and 3. controls who will receive mailed literature. Subjects will have three months to review the content assigned to them (the intervention period) after which they will immediately enter the weight management clinic. Data will be collected at baseline and every 3 months for 9 months (study end), including: 1. Clinical [5% weight loss responders (primary outcome), absolute and % weight losses, changes in obesity-related comorbidities]; 2. Humanistic (health related quality of life, patient satisfaction, depression, and self-efficacy); and 3. Economic (incremental costs and utilities and cost per change in BMI assessed from the third party health care payor perspective) outcomes. Covariate-adjusted baseline-to-nine-month change-scores will be compared between groups for each outcome using linear regression for continuous outcomes and logistic regression for dichotomous ones.

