### Procedures

Two clinics in Alberta, located in Edmonton and Red Deer, will participate in the study, although we have the potential to expand to other bariatric speciality care sites in Calgary, Grande Prairie and Medicine Hat (up to 5 sites total) if needed. Newly wait-listed patients will be contacted by telephone and invited to participate. They will be assessed in-person within 2 weeks of telephone contact to confirm eligibility and provide written consent prior to randomization. Baseline data collection and group specific patient instructions will be provided at this visit. All study participants will be instructed to not begin any other new lifestyle modification or weight-loss related interventions during the first 3 months of the study.

Subjects will be contacted by telephone within 1 week to ensure those allocated to the WWCM have registered for the WWCM sessions (either in-person or web-based) and to address any questions or concerns. Those randomized to the WWCM program will have 3 months to complete the modules. Thereafter, all subjects, including controls, will immediately enter the weight management clinic in their zone to receive multidisciplinary bariatric care. The control group will only receive mailed literature that includes national dietary guidelines. They will receive a phone call at one week reminding them to review the written materials. Although strict patient-level blinding per se will not be possible, subjects will be given general information that the purpose of the study is to examine three different weight management delivery methods to wait-listed patients and more specific information on their assigned treatment group only.

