### Randomization and allocation

Patients will be randomized 1:1:1 to WWCM in-person sessions or WWCM web-based sessions or mailed literature. Computer-generated randomization will be performed centrally and independently by the EPICORE center (http://www.epicore.ualberta.ca) to ensure allocation concealment from all research personnel; randomization will be stratified by participating study centre. Although clinic staff can not be blinded to allocation status, all outcome assessments will be performed by research assistants working independently from regular clinic staff.

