#### Data analysis

Descriptive analyses will be performed and data will be examined graphically and serial changes described. Because these are self-reported data collected every 3 months, we will use a “last-value carried forward” approach to handle missing data as our primary analytic strategy. For example, temporal trends in the SF-12 will be assessed graphically and using analysis of variance (ANOVA) as a test of trends over time. Multivariable, adjusted 9-month changes in continuous measures will be assessed using linear regression in a manner similar to that detailed for the clinical outcome analysis. Patient satisfaction will be categorized as a dichotomous variable [31] and multivariable predictors of deterioration in satisfaction will be determined in serially constructed models.

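### Covariates for the adjusted models are chosen by observed between-arm differences, which in practice leaves out the stratification factor and usually the baseline value

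*Protocol article*

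**What the plan says.** All references are to the protocol article.

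- *Clinical endpoints, Data analysis* sets out three steps, with body weight as the worked example. Response proportions and mean changes are calculated in each arm. Unadjusted tests follow: "chi-square tests will examine for significant differences between cases and controls in 5% response rates", with t-tests for mean weight change. Last, "a multivariable logistic regression model for 5% responders and a linear regression model for mean body weight will be constructed", and covariates enter these models by "adjusting for any statistically significant (P<0.1) or clinically important between group differences".
- *Randomization and allocation* describes central, concealed 1:1:1 allocation and states that "randomization will be stratified by participating study centre". *Procedures* says that "Two clinics in Alberta, located in Edmonton and Red Deer, will participate in the study", with possible expansion to five sites.
- The abstract's *Methods/Design* puts the adjusted comparison forward as the analysis: "Covariate-adjusted baseline-to-nine-month change-scores will be compared between groups for each outcome". It names no covariates.
- *Humanistic endpoints, Data analysis* carries the approach over, assessing adjusted 9-month changes by "linear regression in a manner similar to that detailed for the clinical outcome analysis".

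No section names centre, the baseline value or any other variable as a fixed covariate.

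**The concern.** Covariates belong in a randomised comparison because they predict outcome or were used to constrain the randomisation. This rule uses neither criterion. Both of its routes, the P<0.1 screen and the judgement of clinical importance, require an observed difference between arms. After concealed randomisation such a difference is chance. A strongly prognostic variable that happens to be balanced stays out, and an irrelevant variable that happens to be imbalanced goes in.

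Two variables are affected most. Stratification balances centre by design, so centre will not show the difference that either route needs. The baseline value of a continuous outcome will usually be balanced too.

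The adjusted comparison is what the abstract presents for every outcome. At stake are whether its covariates are known before the data are seen, and how much precision is given up in variables already collected.

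**Working it through.** **1. The plan's own figure.** For 20% versus 35% response, alpha 0.05 two-sided and power 0.90, the standard formula gives 185 per arm with pooled variance and 181 unpooled. This agrees with the stated figure of about 180. The calculation uses no covariates, so changing the adjustment does not alter it.

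**2. How often the screen fires by chance.** Each screened variable has probability 0.1 of P<0.1 under randomisation. For k independent variables, the chance of at least one is 1 − 0.9^k and the expected number is 0.1k.

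| k (assumed) | Expected | At least one |
|---|---|---|
| 5 | 0.5 | 41% |
| 10 | 1.0 | 65% |
| 15 | 1.5 | 79% |
| 20 | 2.0 | 88% |

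The data collection list contains well over ten baseline variables. The article does not say how many will be screened, and they will not be fully independent. A particular baseline value enters by this route about 10% of the time; centre essentially never does.

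**3. Precision for continuous outcomes.** Let rho be the baseline-to-follow-up correlation, with equal variances. Per-patient variance is proportional to 2(1 − rho) for a change score and to 1 − rho² for ANCOVA. The ratio is (1 − rho²) / [2(1 − rho)] = (1 + rho)/2.

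| rho (assumed) | Ratio | Reduction |
|---|---|---|
| 0.4 | 0.70 | 30% |
| 0.5 | 0.75 | 25% |
| 0.7 | 0.85 | 15% |
| 0.9 | 0.95 | 5% |
| 0.95 | 0.975 | 2.5% |

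**4. Simulation, continuous outcome.** Assumed: 220 per arm, two centres split 70:30 and exactly balanced, true difference 0.28 SD. In the rule column, baseline enters only if its own test gives P<0.1; the clinical-importance route was not simulated. The correlation here is between baseline and change. Its square equals (1 − rho)/2 in the notation of step 3, so 0.5 corresponds to rho = 1 − 2(0.25) = 0.5, and 0.3 to rho = 1 − 2(0.09) = 0.82.

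| Baseline-change correlation | Centre effect (SD) | Type I error: rule | Type I error: baseline + centre fixed | Power: rule | Power: baseline + centre fixed |
|---|---|---|---|---|---|
| 0 | 0 | 0.050 | 0.050 | 0.84 | 0.84 |
| 0.3 | 0 | 0.041 | 0.048 | 0.84 | 0.86 |
| 0.5 | 0.5 | 0.035 | 0.048 | 0.84 | 0.92 |
| 0.5 | 1.0 | 0.026 | 0.055 | 0.80 | 0.92 |

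Each null figure rests on 4,000 replicates (standard error √(0.05 × 0.95/4000) ≈ 0.003) and each power figure on 2,000. Over all settings with baseline or centre prognostic, type I error under the rule ran from about 0.026 to 0.042.

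**5. Simulation, binary primary outcome.** Same arm size and centre split, overall response 20% under the null. The plain chi-square is compared with a centre-stratified Cochran-Mantel-Haenszel (CMH) test; power is for a 15-point difference.

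| Response by centre | Type I error: chi-square | Type I error: CMH | Power: chi-square | Power: CMH |
|---|---|---|---|---|
| 20% / 20% | 0.050 | 0.050 | 0.945 | 0.945 |
| 25% / 8.3% (about 17 points apart) | 0.046 | 0.050 | 0.946 | 0.950 |
| 10% / 43.3% (about 33 points apart) | 0.034 | 0.050 | 0.955 | 0.967 |

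**The case against.** The strongest defence is that a journal article condenses, and a full analysis plan may name the covariates. That would answer a complaint about silence, and silence on centre does not show that the full plan ignores the stratification. It does not answer this point: the article states a selection rule outright, and a plan naming fixed covariates would have to depart from it.

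It can also be said that the rule is more than a significance screen, since it admits clinically important differences, and that the text never says the comparisons are at baseline. Both are correct. Baseline is the only sensible reading for choosing covariates, however, and the second route still depends on an observed difference, now with an undefined judgement added.

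Three stronger readings are tempting and are not supported:

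- **The rule inflates false positives.** The simulations show the opposite direction: tests at or below nominal level.
- **The result cannot be set against the 15-point threshold.** The plan calculates response proportions in each arm, so the raw absolute difference is available. Only the adjusted logistic result comes as an odds ratio; for 35% versus 20% that is (0.35/0.65)/(0.20/0.80) = 2.15.
- **The two primary contrasts will carry different covariates.** This is possible if screening is done per contrast, but the wording equally fits one three-arm model with one covariate set.

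The defence is also right that the variance formula says nothing about the binary primary outcome, and that the gain nearly vanishes where follow-up tracks baseline closely, as body weight plausibly does.

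**Conclusion.** The point holds in a limited form. The protocol article fixes its covariates by chance imbalance plus an undefined judgement, for the clinical outcomes and by extension the humanistic ones. In practice this excludes the stratification factor, and in about nine trials out of ten the P<0.1 route excludes the baseline value.

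The consequences are a model that depends on the data and partly on the analyst, lost precision, and somewhat conservative tests when centre or baseline is prognostic. For continuous secondary outcomes the avoidable variance is 15-30% at rho 0.7-0.4 and 2.5-5% at rho 0.95-0.9. In the simulated cases, power moved from about 0.84 to 0.92 with a strong baseline correlation and a centre effect, and not at all when neither was prognostic. For the primary outcome, the effect of ignoring centre is small at a 17-point gap in response between centres and clear only at about 33 points.

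The correlations, centre split, centre effects and number of screened variables are all assumptions; the document gives none of them. This is a change that should be made, but it does not threaten the validity of the trial.

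**What to change.** - Delete the rule that admits covariates on P<0.1 or clinically important differences between arms.
- Prespecify one adjusted model for both primary contrasts: logistic regression of 5% response on arm, centre and baseline weight or BMI, plus at most a few prognostic covariates fixed in advance (sex and diabetes status, for example, are already planned subgroup variables).
- Report the standardised risk difference from that model with its 95% CI, so that the adjusted result, like the raw proportions, can be set against the 15-point threshold.
- For continuous clinical and humanistic outcomes, use ANCOVA with the baseline value and centre.
- Keep the chi-square and t-tests as supportive analyses.

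The cost is wording in the analysis plan, settled before the outcome data are examined. The sample size is unchanged and no new data are needed.

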## Objectives

The EVOLUTION Trial is designed to:

1. Assess the clinical effectiveness of the WWCM program in reducing weight, improving obesity-related comorbidity and decreasing Adult Clinic attrition rates compared to controls.

2. Determine if the WWCM program improves humanistic outcomes including health-related quality of life, patient satisfaction, self-efficacy and readiness-to-change compared to controls.

3. Determine the incremental cost and cost-effectiveness of the WWCM program.

4. Compare the in-person delivery of WWCM content to online delivery in terms of efficacy and cost-effectiveness.

In aggregate, these objectives will assess the program’s impact on a comprehensive range of outcomes important to patients, providers, and policy-makers. Because the WWCM program is intended to prime patients for success as they receive care in the Adult Clinic, the primary outcomes will be measured prior to attending WWCM modules and then repeated six months after entry into the Adult Clinic.

We hypothesize that both online and in-person delivery of the WWCM intervention will reduce body weight and improve clinical and humanistic outcomes at 9 months compared to the control group. Furthermore, we hypothesize that the in-person version of the intervention will be more effective (as a consequence of greater interpersonal contact) but also more costly than the on-line version. Although we hypothesize that the program will be beneficial, this is by no means certain. It is possible that outcomes in the groups receiving the WWCM intervention will be no better than controls, only marginally better, or improved but not in a cost-effective manner. This underscores the need for rigorous program evaluation to ensure that current program delivery - as well as potential future expansion - is warranted.

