**Figure 1 F1:**
[figure not shown]
Study overview.

1. **Sociodemographic data (baseline only):** This includes age, sex, race, marital status, household income and employment status.

2. **Obesity-related comorbidities and past medical history:** includes blood pressure taken with a Watch BP® automated monitor (three readings simultaneously in each arm; first reading discarded and the latter two averaged; higher arm average used as the primary endpoint), fasting lipids and glucose, A1c, creatinine, alanine aminotransferase (ALT) smoking status and cardiovascular medications.

3. **Specific obesity-related variables:** weight, height (using a clinic based stadiometer), BMI.

4. **Quality of life and utility measurement:** Validated generic health related quality of life (SF-12 [35] and EQ-5D [30]) instruments will be used. Preference-based utilities will be measured using the EQ-5D.

5. **Satisfaction with medical care:** assessed using two questions from the Patient Satisfaction Questionnaire (PSQ) [31] that will be scored on a 5-point Likert Scale.

6. **Self-efficacy:** Obesity-specific self-efficacy will be measured using the validated Weight Efficacy Life-Style Questionnaire (WEL), a 20-item instrument that assesses self-efficacy across 5 situational factors (negative emotions, availability, social pressure, physical discomfort and positive activities) [32].

7. **Screening for Depression:** the Patient Health Questionnaire (PHQ-8), a validated screening tool for depression, will be used [33].

8. **Readiness-to-Change:** assessed using a a Visual Analogue scale ranging from 0 to 10.

9. **Attrition Rates (at 6 and 9 months only):** attrition rates within the multidisciplinary clinic will be assessed and compared between study arms.

10. **Costing Data:** Costing will adhere to the three-step micro-costing technique of identification, measurement, and valuation of resources. We will determine the overall and per-patient total and incremental costs of the two versions of the WWCM program and the control arm [34,35]. Start-up costs and on-going program delivery costs for each study arm will be tabulated. The cost per patient will be estimated using the current enrolment in the WWCM, as well as best- and worst-case scenarios (minimal and maximum session capacity) [34,35].

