#### Sample size considerations

Our sample size estimation is based upon the desire to detect a 15% difference between the WWCM interventions and controls in the proportion of 5% weight responders with an alpha level of 0.05 and a power of 0.90. We assume that the enhanced control arm will result in a 5% weight loss in 20% of subjects (i.e., the control event rate = 20% at one year) [38]. Given these parameters, the minimal required sample size will be ~180 patients per arm or 540 patients total (http://statpages.org/proppowr.html). As losses to follow-up have reached 30% in previous obesity related trials; [39] we will also adjust for a 30% potential drop out rate. Therefore, our final estimated sample size will be 220 patients per arm, for a total sample size of 660 patients.

We chose a 5% weight loss threshold as the primary outcome measure of individual patient success (rather than using mean absolute body weight or a similar continuous parameter) based upon the recommendations of current consensus guidelines, which endorse this degree of weight loss as the minimum target to achieve clinically meaningful health benefits after 6–12 months of intervention [10]. We chose a 15% absolute difference between study arms as the minimum clinically worthwhile (important) difference (MCID) by consensus of clinical experts and trials methodologists and have used this type of consensus-based threshold definition in prior studies [40]. We felt that if the WWCM program produced less than a 15% improvement in weight loss [5% response] compared with controls it would not be worth continued funding - unless very compelling benefits on humanistic outcomes or cost-effectiveness were also demonstrated. We partly based our rationale for choosing this threshold on the opinions of prior consensus-based expert panels, that have proposed a 10% MCID for 1-year weight change patients with type 2 diabetes (while recognizing that weight reductions in type 2 diabetics are generally lower than non-diabetics) and a 15% MCID for statin uptake in patients with coronary disease [41,42].

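### The only named check on missing weights, group-mean imputation, cannot test the 5% responder endpoint, and carrying baseline forward is not conservative without qualification

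*Protocol article*

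**What the plan says.** Under Clinical endpoints, Data analysis, the protocol article fixes one rule and one check. The rule: "Missing data for weight change will be addressed using a conservative ‘baseline-value carried forward’ approach". The check: the result is to be "examined in a sensitivity analysis using group mean-imputation methods to confirm the robustness of results". No other method for missing weights is named.

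The endpoint they serve is binary: "We chose a 5% weight loss threshold as the primary outcome measure of individual patient success" (Clinical endpoints, Sample size considerations). That section assumes 20% response in controls, a 15-point difference, alpha 0.05 and power 0.90, and says "we will also adjust for a 30% potential drop out rate".

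Three other statements bear on the point:

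- The first objective includes "decreasing Adult Clinic attrition rates compared to controls".
- Item 9 under Data collection and outcome measures says "attrition rates within the multidisciplinary clinic will be assessed and compared between study arms".
- Randomization and allocation says "all outcome assessments will be performed by research assistants working independently from regular clinic staff".

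Unless otherwise indicated, data are collected at baseline and at 3, 6 and 9 months, and weight is on that list. Neither missing-data rule uses the 3- and 6-month weights.

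**The concern.** A sensitivity analysis is useful only if it varies the assumption behind the main analysis and could give a different answer for a good reason. Group-mean imputation gives every dropout in an arm one value. Once that value is cut at 5%, the whole dropout group moves as a block, so the check either repeats BOCF or shifts an arm's rate by its entire dropout fraction. In neither case does it say how robust the primary result is.

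The label *conservative* raises a second issue. BOCF turns every missing weight into a 0% change, hence a non-response. That weakens a true effect when both arms lose the same share of weights. When one arm loses fewer, that arm gains responders for a reason unrelated to weight. Up to 30% of the primary outcome may be missing, and a 15-point responder difference is tied to continued program funding, so agreement between the two analyses could be read as reassurance it does not give.

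**Working it through.** **Inputs from the article.** Control response 20%; target 35%; alpha 0.05 (two-sided assumed, as sidedness is not stated for this endpoint); power 0.90; 220 per arm; overall loss 30%.

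**Assumptions, not in the article.** Percentage weight change is normal with SD 4, 6 or 8; loss by arm as shown; dropout at random within arm.

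**1. The plan's own figure.** For 20% v 35%, the two-proportion formula gives 185 per arm (pooled variance) or 181 (unpooled), against the stated figure of about 180. The inputs are read correctly.

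**2. Group-mean check at the plan's rates.** The arm mean implied by a response rate p is 5 − SD × z(1−p), with z = 0.842 for 20% and 0.385 for 35%.

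| SD | Mean loss at 20% response | Mean loss at 35% response |
|---|---|---|
| 4 | 1.63 | 3.46 |
| 6 | −0.05 | 2.69 |
| 8 | −1.73 | 1.92 |

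All lie below 5. With 30% loss, 220 × 0.70 = 154 are observed, so the 35% arm's mean sits 0.385 × √154 ≈ 4.8 standard errors below the cut, whatever the SD. Every dropout is imputed as a non-responder, which is BOCF. In 10,000 simulated trials per setting, the two analyses agreed in 100%.

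**3. Group-mean check with means near 5%.** SD 6, equal 30% loss:

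- Both means 5.0: each arm's observed mean is above or below 5 with probability one half, so in about half of trials one arm gains all its dropouts and the other none. Simulated false-positive rate: 26.4% + 25.7% ≈ 52%.
- Both means 4.5: 13.7% + 13.8% ≈ 27%.
- Means 4.5 v 5.5: true response 46.7% v 53.3% (6.6 points); imputed 37.4% v 62.9% (25.5 points).

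**4. Group-mean check on continuous weight change.** With fraction d missing, the arm mean has true variance σ²/[n(1−d)], but the filled-in data suggest about σ²(1−d)/n. The standard error is therefore too small by the factor (1−d), and the test rejects when |Z| > 1.96(1−d):

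- d = 0.20: threshold 1.568, type I error about 12%.
- d = 0.30: threshold 1.372, type I error about 17% (simulation agrees).

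This needs no difference in dropout between arms.

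**5. BOCF.** If dropouts respond like completers, the expected rate is p × (1 − loss), and with no true difference the false gap is p × (loss in control − loss in program). With p = 20% and 220 per arm:

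| Loss, control v program | Rates after BOCF | False gap | Two-sided error |
|---|---|---|---|
| 30% v 30% | 14.0% v 14.0% | 0 | 5.0% |
| 30% v 20% | 14.0% v 16.0% | 2 points | 9.0% |
| 30% v 15% | 14.0% v 17.0% | 3 points | 14.0% |
| 20% v 30% | 16.0% v 14.0% | −2 points | 9.0%, favouring control |

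For the second row, SE = √[(0.14×0.86 + 0.16×0.84)/220] = 0.034 and 0.02/0.034 = 0.59, so the two tails are 8.5% and 0.5%.

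If dropouts respond less often, the gap shrinks. With overall response 20% and dropouts at 10%, 30% v 20% loss gives 0.10 × 0.10 = 1 point and an error of about 6%.

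With equal 30% loss and a true effect, BOCF gives 14.0% v 24.5%: the 15 points become 10.5 and power is about 80%.

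**The case against.** **Clinic attrition is not a missing study weight.** The objective concerns leaving the Adult Clinic, while research assistants independent of clinic staff take the outcomes. A patient can leave the clinic and still be weighed. A reader might infer that the plan itself predicts unequal loss of weights in the program's favour. It does not: no loss by arm is given. The link is likely, not certain, and the splits in step 5 are assumptions.

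**BOCF is defensible.** With equal loss it holds alpha and dilutes the effect, and counting dropout as failure is a recognised estimand. Both points stand, but the article does not state that estimand; it only calls the rule conservative. A 2- to 3-point artefact is also well short of the 15-point funding threshold.

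**The large error rates do not describe the trial.** A reader might take the 27% and 52% in step 3 as the trial's false-positive risk. They belong to a sensitivity analysis, and to arm means outside those implied by 20% and 35% response. The 6% average loss cited in the background for intensive lifestyle care shows that means near 5% are conceivable, but with SD 6 it implies about 57% responders, far from the plan's rates. At the plan's rates the check is uninformative rather than misleading.

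**The article does not say that the mean is imputed and then cut at 5%.** True, and a fuller document may define this. If the arm's responder proportion were imputed instead, the check would return the completers' rates with the sample size overstated, which is still no test of robustness. The standard-error problem for continuous weight change does not depend on this reading.

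**Conclusion.** The point holds in two parts of unequal strength.

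The firmer part is the check. On the responder endpoint it duplicates the main analysis at the plan's own rates (normality and SD 4 to 8 assumed) and becomes erratic if arm means approach 5%. On continuous weight change it is anti-conservative even with equal random dropout.

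The second part is the unqualified word *conservative*. It fails whenever loss of weights differs by arm, in either direction. The 9 to 14% error rests on assumed loss by arm and on dropouts responding like completers; it falls towards 5% as either assumption weakens.

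The documents do not support the stronger conclusion that the primary analysis is invalid or that BOCF must be abandoned. This should be corrected before analysis, but it is not a defect that invalidates the design.

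**What to change.** 1. Replace the group-mean check with multiple imputation of 9-month weight, done separately by arm, using baseline, 3-month and 6-month weights and centre. Derive 5% response after imputation and combine with Rubin's rules. Use the same imputations for continuous weight change.
2. Because multiple imputation assumes that missingness is explained by the data used, add a delta (tipping-point) analysis with separate shifts by arm.
3. BOCF may remain primary if the article states that dropout is counted as non-response. Delete *conservative*, or limit it to equal loss between arms.
4. Show the number of missing 9-month weights by arm beside the primary result. The planned comparison of clinic attrition is a different quantity.

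The cost is a few sentences of text and modest programming. No new data are needed, since the interim weights are already scheduled.
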